# ADHD Remote Technology study of cardiometabolic risk factors and medication adherence (ART-CARMA): a multi-centre prospective cohort study protocol

**DOI:** 10.1186/s12888-022-04429-6

**Published:** 2022-12-20

**Keywords:** Attention deficit hyperactivity disorder, ADHD, Cardiovascular disease, Medication adherence, mHealth, Remote measurement technology, Remote monitoring, Digital phenotyping

## Abstract

**Background:**

Emerging evidence points at substantial comorbidity between adult attention deficit hyperactivity disorder (ADHD) and cardiometabolic diseases, but our understanding of the comorbidity and how to manage cardiometabolic disease in adults with ADHD is limited. The ADHD Remote Technology study of cardiometabolic risk factors and medication adherence (ART-CARMA) project uses remote measurement technology to obtain real-world data from daily life to assess the extent to which ADHD medication treatment and physical activity, individually and jointly, may influence cardiometabolic risks in adults with ADHD. Our second main aim is to obtain valuable real-world data on adherence to pharmacological treatment and its predictors and correlates during daily life from adults with ADHD.

**Methods:**

ART-CARMA is a multi-site prospective cohort study within the EU-funded collaboration ‘TIMESPAN’ (Management of chronic cardiometabolic disease and treatment discontinuity in adult ADHD patients) that will recruit 300 adults from adult ADHD waiting lists. The participants will be monitored remotely over a period of 12 months that starts from pre-treatment initiation. Passive monitoring, which involves the participants wearing a wrist-worn device (EmbracePlus) and downloading the RADAR-base Passive App and the Empatica Care App on their smartphone, provides ongoing data collection on a wide range of variables, such as physical activity, sleep, pulse rate (PR) and pulse rate variability (PRV), systolic peaks, electrodermal activity (EDA), oxygen saturation (SpO2), peripheral temperature, smartphone usage including social connectivity, and the environment (e.g. ambient noise, light levels, relative location). By combining data across these variables measured, processes such as physical activity, sleep, autonomic arousal, and indicators of cardiovascular health can be captured. Active remote monitoring involves the participant completing tasks using a smartphone app (such as completing clinical questionnaires or speech tasks), measuring their blood pressure and weight, or using a PC/laptop (cognitive tasks). The ART system is built on the RADAR-base mobile-health platform.

**Discussion:**

The long-term goal is to use these data to improve the management of cardiometabolic disease in adults with ADHD, and to improve ADHD medication treatment adherence and the personalisation of treatment.

## Background

Attention deficit hyperactivity disorder (ADHD) is a common psychiatric disorder, with a prevalence among adults of 2.5% [1]. The disorder is diagnosed based on impairing levels of inattentive, hyperactive and impulsive behaviours. Most adults with ADHD present with additional serious mental health problems that can include anxiety, depression, emotional instability, antisocial behaviour, substance use and autism spectrum disorder [2]. Emerging evidence further points at substantial comorbidity and shared genetics between adult ADHD and cardiometabolic diseases (obesity, type-2 diabetes mellitus and cardiovascular disease). However, detailed knowledge about the screening, diagnosis and clinical management of adults with ADHD and co-occurring cardiometabolic disease is lacking.

The prevalence of ADHD medication use for adults has increased markedly during the last two decades [3–5]. Randomised control trials (RCTs) on ADHD have shown short-term beneficial effects of ADHD medication on the core symptoms of ADHD [6–8]. However, concerns about the safety of ADHD medications for serious cardiometabolic outcomes have been raised due to reports of cardiovascular disease (CVD) events, including sudden cardiac death, myocardial infarction and stroke in individuals using ADHD medications [9–11]. ADHD medications may also elevate heart rate (HR) and blood pressure [12, 13]. Despite the evidence from the RCTs on short-term beneficial effects, there is a paucity of longer-term, real-world data on the impact of ADHD medication on a wider range of outcomes, as well as of such effects when combined with a non-pharmacological intervention, such as physical activity. The therapeutic effects of physical activity have been described extensively for several psychiatric and cardiometabolic conditions, including depression, sleep problems, obesity, type-2 diabetes mellitus and CVD [14–18]. There is also emerging evidence for positive effects of physical activity on ADHD [19–24], but long-term real-world data are needed, in particular among adults.

Possible reasons for treatment discontinuity in adults with ADHD include lack of treatment response, adverse side effects and poor adherence behaviours (such as forgetting to take the medication). Although sub-optimal response is one of the most common reasons reported for ADHD medication discontinuation, few studies report on adherence and discontinuation results [25]. A systematic review found that of 91 observational studies only eleven studies reported adherence or discontinuation results in adults with ADHD [25]. Side effects reported to ADHD medication include changes to sleep behaviours (such as reduced total sleep time and delayed onset of sleep [26]), reduction in appetite and weight [27, 28]) and hypertension [10, 13, 28]. RCTs or observational studies that rely exclusively on parent/caregiver surveys often do not provide longer-term information about how side effects may influence ADHD medication treatment discontinuity [10, 29]. To improve our understanding of the reasons for treatment discontinuity in adults with ADHD, moment-by-moment quantification of real-world data from the individuals’ daily lives including both active (e.g., completing questionnaires) and passive (e.g., wearable device) monitoring is needed.

Remote measurement technology (RMT) offers new opportunities for collecting detailed, frequent, long-term, real-world data on clinical symptoms, functional and cognitive impairments, physiological measures, health behaviours (such as exercise and sleep) and measures of the environment on large sample sizes. The ADHD Remote Technology (‘ART’) assessment and monitoring system for adults with ADHD, developed by [name], [name] and colleagues [30, 31] utilises this technology and consists of both active and passive monitoring. Active remote monitoring involves the participant completing tasks using a smartphone app (such as completing clinical questionnaires or speech tasks) or using a PC/laptop (cognitive tasks). Passive remote monitoring consists of ongoing data collection using smartphone sensors and a wearable device without active input from the participant; data can be collected on a wide range of variables, such as physical activity, sleep, pulse rate (PR) and pulse rate variability (PRV), systolic peaks, electrodermal activity, oxygen saturation (SpO2), peripheral temperature, smartphone usage including social connectivity, and the environment (e.g. ambient noise, light levels, relative location). The ART system is underpinned by the RADAR-base open-source mobile-health platform [32, 33].

This protocol describes the ADHD Remote Technology study of cardiometabolic risk factors and medication adherence (‘ART-CARMA’), which uses the ART system. ART-CARMA is a clinical study within the EU-funded collaboration ‘TIMESPAN’ (Management of chronic cardiometabolic disease and treatment discontinuity in adult ADHD patients), which unites a multidisciplinary team of 17 partners from academia, small and medium-sized enterprises (SMEs), patients and care providers. The main objective of TIMESPAN is to advance the management of adult ADHD and co-occurring cardiometabolic disease by improving the identification and treatment of individuals with these comorbidities. The wearable device included in ART-CARMA is the EmbracePlus developed by the SME partner Empatica [34]. ART-CARMA will use RMT in adults with ADHD to carry out unobtrusive, real-time data collection over a period of 12 months. By recruiting 300 adults from adult ADHD clinic waiting lists and monitoring them remotely, we will obtain objectively measured data relevant to cardiometabolic risk profiles from the patient’s daily life, both on and off pharmacotherapy. By targeting the informative period from pre-treatment initiation through to treatment initiation, titration and the subsequent period, up to 12 months in total, we will obtain real-time data on multiple parameters, including side effects, that aims to inform future personalisation of treatment.

### Patient involvement in the ART-CARMA study protocol

The ADHD Remote Technology (ART) system benefits from procedures developed in the RADAR-MDD study protocol [35]; a RMT study that recruited over 600 individuals with major depression disorder (MDD), over a 24-month remote monitoring period. RADAR-MDD underwent extensive development in collaboration with service-users to promote the design of acceptable and feasible RMT tools [36]. In addition, study participants from our initial ART pilot study provided feedback on the acceptability of measures and procedures piloted in that study [31]. In ART-pilot, 95% of the participants agreed that there is value in gathering data through RMT, with some participants explaining passive monitoring provides a unique opportunity to collect objective data. All participants with and without ADHD (100%) agreed that the study measures blended into their daily life, and 82% of participants were positive about using the system for at least one year. We have incorporated improvements to the ART-CARMA study design that were suggested by the participants in ART-pilot, such as longer intervals between the administration of the cognitive tasks during the remote monitoring period. We also ran a service-user focus group that further informed this study design regarding the frequency of questionnaire administration and the acceptability of additional measures included in ART-CARMA that were not included in ART-pilot. We have incorporated suggestions from TIMESPAN partners [name] and [name]. [name], a patient advocate for people with ADHD, founder and Chief Executive of Attention Deficit Disorder Information Services (ADDISS), has provided input to the ADHD remote measure development via the wider ART research programme (on which she is an external collaborator). She has provided further input into the ART-CARMA study protocol specifically during the initial planning stage. [name], executive director of the European Association for the Study of Obesity (EASO) has been involved in the project outline.

### Study objectives

The first main aim (objectives 1–3 below) is to obtain real-world data from the patient’s daily life on the extent to which ADHD medication treatment and physical activity, individually and jointly, may influence cardiometabolic risks in adults with ADHD. This will provide new insights into disease patterns and help improve the safety and effectiveness of pharmacological (i.e., ADHD medication treatment) and non-pharmacological (i.e., physical activity) interventions for patients with ADHD and co-occurring cardiometabolic disease. The second main aim (objectives 4–6 below) is to obtain in vivo, real-world data from the patient’s daily life on adherence to pharmacological treatment and its predictors and correlates, over a remote monitoring period of 12 months that starts from pre-treatment initiation. The long-term goal is to use these data to improve the management of cardiometabolic disease in adults with ADHD, and to improve ADHD medication treatment adherence and the personalisation of treatment.

ART-CARMA has six specific objectives:Objective 1: Use RMT to identify real-world consequences of ADHD medication treatment on the following cardiometabolic risk (or protective) factors in adults with ADHD: changes in HR, blood pressure, weight, smoking, alcohol use, diet, sleep and physiological stress response.Objective 2: Use RMT to measure the potential contribution of physical activity to a reduction in these risk factors, independently and in combination with ADHD medication treatment.Objective 3: Use machine learning, applied to the full set of multimodal remote monitoring data from the 12-month period, to build prediction models of the cascade of effects that follow from the initiation of ADHD medication treatment. This allows us to go beyond objectives 1 and 2, to obtain insight into potential underlying mechanisms that are needed for developing algorithms for personalised treatment. The prediction models allow us to assess complex, temporal relationships between multiple measures.Objective 4: Use RMT to explore ADHD medication use patterns in adults with ADHD in the first year of starting ADHD medication treatment (including treatment initiation, titration and the subsequent period) and to quantify the extent of treatment adherence, non-adherence and treatment gaps.Objective 5: Use RMT to identify potential reasons for non-adherence, with a focus on adverse side effects (e.g. daytime sleepiness and changes in electrodermal activity indexed arousal/alertness, changes in heart rate or blood pressure, changes in appetite/weight, increased anxiety/depressive symptoms or irritability, not feeling themselves/feeling their personality changes when on medication, tics, dizziness, sweating, headaches), lack of treatment response (limited or no effect on ADHD symptoms and impairments) and poor adherence behaviours (e.g. forgetting to take or difficulties taking ADHD medication). We capture these time series data across the periods of pre-treatment, treatment initiation, titration and subsequent monitoring.Objective 6: Identify psychiatric comorbidities that predict treatment non-adherence or increase adverse effects. We will measure symptoms of autism spectrum disorder, antisocial behaviour, anxiety, depression and substance use.

## Methods

### Study design

ART-CARMA is a clinical study being undertaken as part of a larger body of work by the Management of chronic cardiometabolic disease and treatment discontinuity in adult ADHD patients (TIMESPAN [37]) research consortium. Below is a summary of the methods used in ART-CARMA.

ART-CARMA is a prospective observational non-randomised, non-interventional study, using wearable technology and smartphone sensors, representing no change to the usual care or treatments of participants due to participation. There is no control comparison group, or randomised group allocation.

### Study population

Power calculations (GPower 3.1) for a regression analysis with five predictors indicate that a sample size of 280 has 80% power (alpha 0.01) to detect a small effect size (f2) of 0.07. Published Monte-Carlo simulations that aimed to determine the necessary sample size to achieve stable estimates for correlations suggest that, in typical scenarios, a sample size of approx. 250 is required for stable estimates [38]. These considerations, together with the evidence that has accumulated from the RADAR-MDD remote monitoring study regarding potential challenges with RMT protocols (e.g., attrition, missing data) ([39]), have led to the proposed sample size of 300. The eligibility criteria for inclusion in this study are summarised in Table 1.

**Table 1 Tab1:** Eligibility criteria for participation in ART-CARMA

ADHD group inclusion criteria	Diagnosis of DSM-5 ADHD
	Aged 18–60
	Able to give informed consent for participation
	Fluent in English
	Willing and able to complete self-reported assessments via smartphone
	Willing to use either their own Android phone or a study Android phone as their only smartphone during the data collection period
	Willing to wear the wearable device (EmbracePlus) during the data collection period
	Not on ADHD medication at the time of recruitment
ADHD group exclusion criteria	Psychosis, currently experiencing a major depressive episode, mania, drug dependence over the last six months or a major neurological disorder
	Recent contact with psychiatric acute care (admission, crisis team or liaison team (A&E)) in the last six months
	Any other major medical disease which might impact upon the patient’s ability to participate in normal daily activities (e.g., due to hospitalisations)
	Does not start ADHD medication following ADHD diagnosis (either due to personal choice or psychiatrist deciding not to prescribe ADHD medication)
	Pregnancy
	IQ < 70
Partner, family member or close friend group inclusion criteria	A parent, partner or a close friend, as chosen by the participant with ADHD
	Aged 18 or over
	Willing and able to complete web-based questionnaires regarding the participant with ADHD

*DSM-5* The Diagnostic and Statistical Manual of Mental Disorders, Fifth Edition, *IQ* intelligent quotient

### Study procedures

Participants will be recruited over twenty-four months across two data collection sites of ART-CARMA at King’s College London (UK) and Vall d’Hebron Research Institute (Spain). In total, across the two sites, we will recruit 300 adults from adult ADHD clinic waiting lists, which enables an initial off-medication remote monitoring period and subsequent continuous remote monitoring following initiation of ADHD medication treatment. The schedule of events is available in Table 2. The flow of participants through the study, including reasons for not participating in the study, will be standardised across sites and documented in a flowchart (Fig. 1).

**Table 2 Tab2:** Schedule of events for ART-CARMA

Month	0		1	2	3	4	5	6	7	…	11	12
Assessment	1	2	n/a	n/a	n/a	n/a	n/a	n/a	n/a	n/a	n/a	n/a
Baseline assessments												
Study explanation (WR)	X											
Informed consent (WR)	X											
Introductory training (WR)		X										
ADHD diagnostic interview DIVA-5 (WR)	X											
Psychiatric comorbidities MINI (WR)	X											
IQ and working memory WASI-II and WAIS-IV (WR)	X											
Socio-demographics, medical history, service use, experience with technology (R/WR)	X											
Autism Spectrum Disorder AQ-10 (R/WR)	X											
Cognitive tasks (WR)		X						X				X
Physical measures of weight and waist circumference (WR)		X										
Blood pressure (WR)		X										
DNA saliva sample		X										
Microbiota sample		X										X
Remote data collection												
Wearable sensors			Continuous (months 1-12)									
Smartphone sensors (pRMT)			Continuous (months 1-12)									
Medication use (aRMT)			Continuous (months 1-12)									
Medication side effects CADDRA Patient ADHD Medication Form (aRMT)			XX XX	XX XX	XX XX	XX XX	XX XX	XX XX	XX XX	XX XX	XX XX	XX XX
ADHD BAARS-IV – self-report (aRMT)		X	X	X	X	X	X	X	X	X	X	X
Anxiety GAD-7 (aRMT)		X	X	X	X	X	X	X	X	X	X	X
Depression PHQ-8 (aRMT)		X	X	X	X	X	X	X	X	X	X	X
Aggression RPQ-A (aRMT)		X	X	X	X	X	X	X	X	X	X	X
Irritability ARI – self-report (aRMT)		X	X	X	X	X	X	X	X	X	X	X
Weight and waist circumference (aRMT)		X	X	X	X	X	X	X	X	X	X	X
Blood pressure (aRMT)		X	X	X	X	X	X	X	X	X	X	X
Smoking Test Fagerstrom (aRMT)		X	X	X	X	X	X	X	X	X	X	X
Alcohol use AUDIT (aRMT)		X	X	X	X	X	X	X	X	X	X	X
Diet 14-item Mediterranean diet adherence questionnaire (aRMT)		X	X	X	X	X	X	X	X	X	X	X
Speech sample task (aRMT)		X	X	X	X	X	X	X	X	X	X	X
Major life events LTE (aRMT)		X						X				X
ADHD BAARS-IV – other report (R)		X	X	X	X	X	X	X	X	X	X	X
Irritability (ARI – informant report) (R)		X	X	X	X	X	X	X	X	X	X	X

*WR* With researcher either in-person or virtually, *R* REDCap web-based platform, *pRMT* Passive App, *aRMT* Active App. X delivered once per month. XX delivered twice per month (every 2-weeks). XXXX delivered four times per month (every week)

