**Fig. 1 Fig1:**
[figure not shown]
Participant flowchart

Recruitment procedures will vary slightly across the two sites. Adults will be recruited who are on the waiting list and are not yet receiving ADHD medication. In the UK/British Isles, the clinical team will contact the individuals by their preferred method of contact (post, email, or telephone) and will provide them with information about the study. If the patient is interested in taking part, the first baseline assessment with the research team will be scheduled. The participant information sheet and informed consent form will be sent to patients a minimum of 24 h before the baseline assessment. In Spain, individuals will be provided with information about the study on the day of their ADHD assessment. If the patient is interested in taking part, the baseline assessments will be completed on the same day. Written informed consent will be obtained.

The baseline assessments will happen either in-person or virtually using Microsoft Teams depending on the site they have been recruited from. In the UK/British Isles, participants will be paid £30 at the point of enrolling in the study, and a further £5 for every completed outcome measure (paid at months 6 and 12). Participants will be paid an additional £30 at the end of the study period (month 12). In Spain, participants will not receive any financial compensation for their participation.

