#### Active App

Participants will be asked to download the RADAR-base Active App that requests the participant to complete questionnaires at specific intervals. Every day participants will be asked to complete a short questionnaire for medication use on whether the participant took their medication that day, with follow-on questions on type and dose of medication or why medication was not taken (e.g., experienced side effects, forgot to take their medication, or chose not to take their ADHD medication that day). Every week participants will be asked to report their medication use side effects using the CADDRA Patient ADHD Medication form [45]. This form contains four items on changes experienced since starting medication and 28 items on side effects. Every four weeks, participants will be asked to complete a longer set of questionnaires: ADHD symptoms and impairments will be measured using the Barkley Adult ADHD Rating scale on current symptoms (BAARS-IV) [46] and Barkley ADHD functional impairment scale [46]. This includes the 18 diagnostic ADHD symptoms and 10 items on functional impairment; Depression will be measured using the 8-item Personal Health Questionnaire Depression Scale; PHQ-8 [47], which is a widely used measure of current depression in the general population; Anxiety will be measured using the 7-item Generalized Anxiety Disorder questionnaire; GAD-7 [48], which provides a dimensional score of anxiety symptoms; Aggression will be measured using the 23-item Reactive-Proactive Aggression Questionnaire for Adults; RPQ-A [49]; Irritability will be measured using the self-reported 7-item Affective Reactivity Index questionnaire; ARI-s [50]; Smoking behaviours will be measured the 6-item Test Fagerstrom questionnaire [51]; Alcohol use will be measured using the Alcohol Use Disorders Identification Test; AUDIT [52]; Diet will be measured using the 14-item Mediterranean diet adherence questionnaire [53]; Blood pressure and weight measurements will also be taken. Participants will be provided with an Omron M2 Basic blood pressure monitoring machine, weighing scales and a tape measure; Major life events will be measured every 6 months using the 13-item List of Threatening Experiences; LTE [54]. The participant will also be asked to complete a short speech task monthly, on the Active App.

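### The weekly side-effect form has no month-0 delivery, so participants who start medication before their first completed form have no pre-treatment score for items such as headaches, dizziness, tics and sweating

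*Protocol article*

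**What the plan says.** All references are to the protocol article.

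- **Table 2 (Study procedures).** The row "Medication side effects CADDRA Patient ADHD Medication Form (aRMT)" has both month-0 cells empty and carries four marks in every month from 1 to 12. The table key reads "XXXX delivered four times per month (every week)". The Active App section also describes the form as weekly.
- **Other Active App rows.** Most have an entry at month 0, assessment 2, and then repeat; "Anxiety GAD-7 (aRMT)" is an example. The row "Medication use (aRMT)" also has no month-0 entry and is shown as continuous over months 1 to 12. The Active App section says of it: "Every day participants will be asked to complete a short questionnaire for medication use on whether the participant took their medication that day".
- **Content of the form (Active App).** It has "four items on changes experienced since starting medication and 28 items on side effects". The article does not make the form conditional on treatment having begun.
- **Objective 5 (Study objectives).** After listing side effects, lack of response and poor adherence behaviours, it states: "We capture these time series data across the periods of pre-treatment, treatment initiation, titration and subsequent monitoring".
- **Timing.** Table 1 requires participants to be unmedicated at recruitment. Remote monitoring begins straight after the baseline assessment. Study procedures say that waiting-list recruitment allows an initial off-medication period, but give it no minimum length. In Spain, "individuals will be provided with information about the study on the day of their ADHD assessment", and the baseline assessments are completed that same day.

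**The concern.** Headaches, dizziness, sweating and tics can be present before any drug is taken. The study has no control group, so a participant's own pre-treatment level is the main reference for judging whether a complaint appeared or worsened after treatment began. Where that level was never recorded, a long-standing complaint and a new one look the same.

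The study does not alter usual care, so it does not control when medication starts. The pre-treatment score therefore depends on a weekly form arriving, and being completed remotely, before the first dose. For most of the other app measures it is secured in the baseline session. This is a question of data collection: no later analysis can recover a score that was not taken.

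**Working it through.** The article gives no figure to reproduce on this point. The check is a count of the schedule followed by a reading of the timing.

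**1. Active App rows in Table 2.** There are 14: medication use, side-effect form, BAARS-IV self-report, GAD-7, PHQ-8, RPQ-A, ARI self-report, weight and waist, blood pressure, smoking, alcohol, diet, speech task, life events.

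- With a month-0 entry: 12.
- Without: 14 − 12 = 2, namely medication use and the side-effect form.

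Medication use at entry is already known to be nil from Table 1, so its empty cell loses nothing. The side-effect form's empty cell does.

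**2. Which Objective 5 side effects have another month-0 measure?**

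| Side effect in Objective 5 | Month-0 measure in Table 2 |
|---|---|
| Anxiety | GAD-7 |
| Depressive symptoms | PHQ-8 |
| Irritability | ARI, self and informant |
| Weight | Yes |
| Blood pressure | Yes |
| Headaches, dizziness, tics, sweating | No row labelled for them |

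The exposure is confined to items like those in the last line.

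**3. Who lacks a pre-treatment score?** Let T be the day of the first dose and F the day of the first completed weekly form, both counted from baseline.

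- If T is later than F, at least one pre-treatment score exists.
- If T is on or before F, none can be relied on.

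The article does not give the delivery day of the first form. If it comes at the end of week 1 (an assumption), F is about day 7. If it comes on day 1, the gap almost closes. Each missed form moves F back by 7 days.

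**4. How many?** The article gives no distribution of time from baseline to first dose at either site, so the share with T on or before F cannot be computed. Per percentage point of the planned sample: 0.01 × 300 = 3 participants.

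**5. Against the stated aim.** Objective 5 says the series includes the pre-treatment period. With no minimum off-medication period and no month-0 form, the schedule makes this likely for most participants but secures it for none.

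**The case against.** The strongest reply is that pre-treatment forms are already scheduled. Participants enter unmedicated from waiting lists, monitoring starts at once, and the form is weekly and not tied to treatment. The rows that begin at month 1 are those collected continuously or weekly, so the empty cell may only reflect a layout convention. This largely stands, and it limits the gap to starts before the first completed form. It does not close the gap, because no minimum off-medication period is stated.

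A reader might infer four stronger things that the document does not support:

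- **That every complaint will be counted as a drug effect.** No such rule is stated, and Objective 5 describes a series running from before to after initiation. Misattribution is a risk only for participants with no earlier score.
- **That irritability, anxiety, depression, weight and blood pressure are also exposed.** They have their own month-0 measures.
- **That the loss falls mainly on the Spanish site.** Same-day baseline makes an early start plausible there, but the article does not say when medication begins at either site.
- **That side-effect frequencies would be inflated several-fold across the cohort.** A count with no baseline overstates the excess by p1/(p1 − p0), where p0 and p1 are the pre-treatment and on-treatment frequencies. Under assumed values this is 0.30/(0.30 − 0.20) = 3, 0.50/(0.50 − 0.40) = 5, or 0.60/(0.60 − 0.20) = 1.5. The result depends on the assumption, applies only to participants without a baseline, and cannot be scaled up without knowing their share.

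It is also fair to say that handling the four change items before treatment is app configuration, which an article may leave to the full protocol. That handling is therefore part of the remedy here and not a separate fault.

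**Conclusion.** The concern holds in a limited form. The side-effect form is one of two Active App rows without a month-0 entry, and the only one of the two for which a pre-treatment level is informative. Participants who start medication before their first completed weekly form will have no pre-treatment score for items with no other baseline measure, and complaints they already had may be misattributed. This falls short of what Objective 5 states.

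The window is about one week, assuming that the first form arrives at the end of week 1 and is completed. It is shorter if the form arrives sooner and longer if forms are missed. The number affected is unknown and may be small. The change is still worth making, because the missing score cannot be recovered, there is no control group to stand in for it, and the remedy is cheap.

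**What to change.** 1. In Table 2, add a month-0 (assessment 2) delivery of the 28 side-effect items.
2. Show the four items on change since treatment began only after the first dose logged in the daily medication questionnaire, and say so in the Active App section.
3. State that the month-0 score is the pre-treatment reference for each item.

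The cost is one more form per participant, in a session that already includes app questionnaires and training, plus one display rule in the app. The downside is a few extra minutes in a baseline of about four hours. Treatment and the later schedule are unchanged.
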